### Participants

#### Inclusion criteria

The following criteria must be met for inclusion: (1) patients aged between 19 and 80 years old; (2) patients with first-ever stroke, with a time since stroke onset ≤ 3 months; (3) patients with unilateral right or left-sided stroke; (4) patients with a Mini-Mental State Examination score > 24 [26]; (5) patients with at least minimal antigravity movement in the affected upper limb; (6) patients with at least 5 degrees of wrist extension in the antigravity position; (7) patients without hemi-spatial neglect; and (8) patients who sign the informed consent form.

#### Exclusion criteria

The following criteria will result in exclusion: (1) any active uncontrolled medical, cardiovascular, or orthopedic condition; (2) significant upper limb peripheral neuropathy; (3) severe shoulder pain or wrist and finger contractures; (4) contraindication to FES, such as a skin allergy; and (5) currently participation in any other clinical study or coach-directed exercise program.

### Setting and recruitment

A total of 162 individuals who comply with the inclusion criteria will be recruited from the Seventh People's Hospital of Shanghai University of Traditional Chinese Medicine and neighboring communities using flyers, posters, and referrals from a rehabilitation therapist or neurologist. The participants will be invited to undergo an in-person examination and evaluation to guarantee that they satisfy the inclusion criteria and fail to meet the exclusion criteria. In addition, we will inform all participants of the study's purpose, methodology, and prospective benefits, as well as the principle of voluntary participation. All participants will be asked to provide written informed consent. Recruitment began on 1 May 2023 and will continue until 162 individuals are enrolled.

### Randomization, allocation concealment and blinding

To minimize any potential bias, the eligible participants will be randomly assigned to 3 groups using stratified randomization with sex (male/female), stroke type (hemorrhage/infarction) and dominant hand (left/right) as factors [27]. After categorization, there will be eight subgroups: (1) male, hemorrhage, left hand dominant; (2) male, hemorrhage, right hand dominant; (3) male, infarction, left hand dominant; (4) male, infarction, right hand dominant; (5) female, hemorrhage, left hand dominant; (6) female, hemorrhage, right hand dominant; (7) female, infarction, left hand dominant; (8) female, infarction, right hand dominant. For any one subgroup, the participants will be randomly divided into groups A, B, and C; then, all A, B, and C groups will be merged to form new group A, B, and C groups. The randomization number lists will be generated by the random number generator of SPSS software (IBM Corp. Released 2013. IBM SPSS Statistics for Windows, Version 22.0. Armonk, NY: IBM Corp.).

The allocation of participants will be secured in opaque numbered and sequentially sealed envelopes, which will be prepared by an independent researcher. The corresponding envelopes will be opened to ascertain a patient’s group assignment after all baseline assessments have been completed by the participants. In addition, physiotherapists with the same level, robotic and FES operators will also follow randomization and be randomly assigned to one of the groups.

The outcome assessors and statisticians who implement the final statistical analyses will be blinded to avoid any potential detection bias.

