## Methods

### Study design

This will be a single-center, assessor-blinded randomized controlled trial (RCT) involving a 12-week intervention and 6-month follow-up. A total of 162 patients with stroke will be recruited and randomly assigned to the FES + CRP group, RAT + CRP group and FES-RAT + CRP group at a ratio of 1:1:1. Figure 1 depicts a concise flowchart of the entire study, and Table 1 provides the schedule of events. The study protocol (2023-7th-HIRB-034) was approved by the Ethics Committee of the Seventh People's Hospital of Shanghai University of Traditional Chinese Medicine and registered in the Chinese Clinical Trial Registry (ChiCTR2300071588).

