### Sample size calculation

The G*power software was utilized to determine the minimum sample size required to detect a significant between-group difference in the present research [24]. In a study of RAT for upper-extremity poststroke rehabilitation, Takebayashi et al. [25] used the minimal clinically significant difference as a reference (4.25 points), the mean difference in the FMA-UE score between patients in the RAT and CRP was 4.50 points and standard deviations between patients were 6. Based on a prior two-way repeated analysis of variance (ANOVA) F test, with a power of 0.80, an effect size of 0.158, three groups, five measurements, correlation among repeated measures of 0.5, and an alpha level of 0.05, 129 participants were required for this study. To account for a conservative drop-out rate of 20%, the final sample size will therefore be 54 participants in each group, for a total of 162 participants.

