### Statistical analysis

All statistical analyses will be performed with IBM SPSS (IBM Corp. Released 2013. IBM SPSS Statistics for Windows, Version 22.0. Armonk, NY: IBM Corp.) by statisticians who are blinded to the group allocation. The analyses will be performed on an intention-to-treat basis. The Shapiro–Wilk (SW) test will be used to examine the normal distribution of the continuous variables comprising demographic and outcome measures. Continuous variables will be described as the mean ± SD for those with normal distributions or the median for those with nonnormal distributions, and categorical variables will be described as the frequency. The χ^2^ test or Fisher’s exact test will be used to examine the comparisons among the three groups for categorical variables. When the normality of data distribution is determined, two-way of variance with repeated measures will be applied to examine the main effects of the group and time factors, as well as the group-time interaction effects. A simple effect post hoc analysis will be conducted when the time-group interaction is significant. Furthermore, the linear mixed model will be adjusted for age, sex and type of stroke if homogeneity is not found. The significance level for all statistical tests will be set at 0.05, corrected for multiple comparisons using the Bonferroni-adjusted method and accompanied by a 95% confidence interval.

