We recognize that this study also has limitations. This research has an inevitable limitation associated with the difficulty in controlling the methodology of blinding during the RAT intervention because the participants and therapists cannot be blinded due to the visibility of the RAT intervention. Although the outcome assessors and data analyzer will be blinded to the group allocation, there might still be a risk of detection bias during the study’s implementation. Additionally, muscle synergy extraction, FES and RAT training in this study need to be performed by medical personnel in medical institutions, which may limit the promotion and application of synergy-based FES and RAT in the community and home settings. Furthermore, based on the results of a few recent studies, there were no differences between intracerebral hemorrhage and cerebral infarction of function prognosis at rehabilitation discharge, so when including patients, we didn’t make a clear distinction on whether different types of strokes will affect the intervention outcomes, which should be investigated in further study.

In summary, the results of the study protocol will achieve multiple study purposes, including demonstrating the effectiveness of synergy-based FES, and synergy-based FES-RAT for improving upper limb function after stroke and exploring the efficacy differences in improving upper limb function after stroke between the FES-RAT therapy and FES or RAT. Synergy-based FES combined with RAT may have a potential opportunity to better improve the upper limb function of stroke survivors. These results of the study will provide high-quality evidence for integrated synergy-based FES and RAT and synergy-based FES alone and guide the design of more effective treatment methods for stroke rehabilitation.

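### Time since stroke onset, open from entry up to 3 months, is neither a stratifier nor a listed covariate; unconditional adjustment for it would gain precision at almost no cost

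*Protocol article*

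**What the plan says.** Four places in the protocol article bear on this.

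- **Inclusion criteria.** Entry is for "patients with first-ever stroke, with a time since stroke onset ≤ 3 months". No minimum is given.
- **Randomization, allocation concealment and blinding.** Patients are allocated "using stratified randomization with sex (male/female), stroke type (hemorrhage/infarction) and dominant hand (left/right) as factors". The eight resulting cells are listed one by one, so the list of factors is complete as stated.
- **Statistical analysis.** The main method is a two-way repeated-measures analysis of variance. On covariates the plan says that "the linear mixed model will be adjusted for age, sex and type of stroke if homogeneity is not found". Time since onset is not named.
- **Sample size calculation.** The between-patient SD of the FMA-UE is taken as 6 points, the reference minimal difference as 4.25 points, and the final size as 54 per group.

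**The concern.** With a 12-week treatment period and entry up to 3 months after onset, patients are treated at quite different stages after stroke. If natural arm recovery slows as time passes, part of each patient's FMA-UE change depends on when they entered, whatever the arm. Time since onset appears in neither of the two places where a plan can deal with such a factor, the randomisation and the model.

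The covariate rule does not close the gap. It is conditional on a homogeneity check, and its list omits time since onset. Even if the arms were seen to differ in onset time, the stated rule would adjust for age, sex and stroke type only.

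The precision of the comparisons between FES-RAT and FES or RAT alone (Aim 3) is at stake. All three arms receive conventional rehabilitation plus an active component, so avoidable noise in these comparisons should be removed where that is cheap.

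**Working it through.** **Inputs from the protocol article**
- Entry window: up to 3 months, taken as 90 days (Inclusion criteria).
- SD 6 points; 129 required and 20% dropout (Sample size calculation). Check of the final size: 129 / (1 − 0.20) = 161.25, rounded up to 162, or 54 per arm. How the 129 was obtained plays no part below.

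**Assumptions (not in the documents)**
- Onset-to-entry time is uniform over 0 to 90 days.
- Expected FMA-UE gain falls linearly by 5, 10 or 15 points from the earliest to the latest entrant.
- The SD of 6 applies to the compared outcome and already includes the variation due to timing.

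**Step 1. Spread due to timing.** SD of onset time = 90 / √12 = 26.0 days. In points, the SD is 5/√12 = 1.44, 10/√12 = 2.89 or 15/√12 = 4.33.

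**Step 2. Residual SD after adjustment** = √(6² − timing SD²).

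**Step 3. Standard error of a pairwise difference** = SD × √(2/54) = SD × 0.1925. Unadjusted: 6 × 0.1925 = 1.15.

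| Assumed difference in gain across window | Timing variance | Share of 36 | Residual SD | SE, adjusted | Unadjusted n per arm giving the same SE |
|---|---|---|---|---|---|
| 5 points | 2.08 | 5.8% | 5.82 | 1.12 | 54/0.942 = 57 |
| 10 points | 8.33 | 23.1% | 5.26 | 1.01 | 54/0.769 = 70 |
| 15 points | 18.75 | 52.1% | 4.15 | 0.80 | 54/0.479 = 113 |

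**Step 4. Chance imbalance.** The standard error of a difference in mean onset time between two arms is 26.0 × √(2/54) = 5.0 days, so the 95% range is ±9.8 days. Multiplied by 5, 10 or 15 points per 90 days, this shifts an arm difference by ±0.54, ±1.09 or ±1.63 points. These are 95% limits, not maxima. In simulation, ignoring the existing strata, the largest of the three pairwise gaps exceeded 7 days in about 34% of randomisations, with a 95th percentile of 11.7 days.

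**Step 5. Steps 3 and 4 describe the same variance.** One standard error of the shift is 0.28, 0.56 or 0.83 points. For the middle case, 1.01² + 0.56² ≈ 1.33 = 1.15². The imbalance is therefore already inside the unadjusted standard error of 1.15 and must not be added to it.

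**Step 6. Power.** For 4.25 points with 43 per arm (129/3) and alpha 0.05/3, pairwise power is 0.81 at SD 6. If timing explained an assumed 5% to 40% of variance, it would be 0.84 to 0.97. The first two rows of the table lie within that range of explained variance; the third lies beyond it.

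**Sensitivity.** If the SD of 6 came from a population without this spread in timing, the unadjusted SD here would be √(36 + 2.08) = 6.17, √(36 + 8.33) = 6.66 or √(36 + 18.75) = 7.40, and adjustment would bring it back to 6.

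**The case against.** **Randomisation already protects the comparison.** This stands. Allocation is concealed, onset time is balanced in expectation, and the confidence interval covers chance imbalance. With an SE of 1.15 the unadjusted 95% range is about ±2.3 points, and the shifts in step 4 lie within it. A reader might infer that an excess of early patients would bias the trial; the documents do not support that.

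**The size rests on assumptions.** This also stands. No section gives a recovery slope or a distribution of onset times. A reader might picture patients entering on the day of the stroke, since no minimum is stated. The cognitive score, arm movement, wrist extension and consent requirements, and recruitment partly by flyers and referral, make very early entry unlikely. A narrower spread shrinks the timing SD in proportion. Nor do the documents rank onset time above other factors such as baseline FMA-UE, so it cannot be called the main source of variation.

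**The existing stratifiers are defensible.** A reader might infer that the authors stratify on a factor they regard as irrelevant, because the Discussion says that "there were no differences between intracerebral hemorrhage and cerebral infarction of function prognosis at rehabilitation discharge". That sentence rests on a few recent studies and one time point, and the authors leave the effect of stroke type on intervention outcomes to further study. Stratifying on an unresolved factor is reasonable caution.

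**A fuller covariate list may be in the SAP.** That is possible. But the article does name its covariates and the condition for using them, and that stated rule is what can be improved.

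**Conclusion.** The point holds as a matter of precision. Time since onset is handled neither in the randomisation nor in the stated covariate rule, although entry is open across 3 months. Under the stated assumptions, adjustment would cut the standard error of a pairwise FMA-UE difference by about 3%, 12% or 31% (from 1.15 to 1.12, 1.01 or 0.80). At the low end the gain is slight; at the high end it is worth more than doubling the sample. Which applies depends on a slope and a spread of onset times that the documents do not give, and on how well a linear term captures recovery.

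The validity of the randomised comparison is not in question, and no case is made for a different stratifier. Recruitment began on 1 May 2023, so changing one now would leave two allocation schemes in one trial, while covariate adjustment gives most of the benefit for every patient.

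**What to change.** In Statistical analysis, prespecify days from stroke onset to randomisation as a covariate in the main FMA-UE mixed model, for all patients and regardless of any homogeneity check. Include its interaction with visit: a covariate effect that is constant over visits would leave the group-by-time contrasts unchanged, whereas differing natural recovery shows up as a different change over time. Fix the form of the term (for example linear in days) before unblinding.

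No new data are needed, because the onset date must be known to confirm eligibility. The covariate is fixed at entry, so treatment cannot affect it, and patients already randomised are covered. The cost is model degrees of freedom: one main effect plus one interaction term for each visit after the first, at most 1 + 4 = 5 parameters over five visits, against 162 patients. The stratification stays as it is.

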### Functional electrical stimulation (FES)

A synergy-based multi-channel FES device was developed using the Fourier ElectroFortis Programmable Stimulator, which can stimulate multiple muscles with customized parameters. An experimenter computer GUI application was created to configure the following basic stimulation parameters: the frequency, minimum and maximum intensity, pulse duration, ramp time, synchronization and order of stimulations, type of user interactions and number of repetitions [30]. The stimulation envelope will be specified as the concatenated piecewise linear functions (e.g., rising phase, plateau phase and falling phase), and will be allowed to be preloaded to the FES device [11]. Synergy-based FES will be applied to stroke participants and constructed from the muscle synergies of healthy controls. The raw EMG signals of the dominant upper limb muscle will be obtained from healthy controls performing the RTG task [31]. After processing with a filter and rectification, the muscle synergy pattern will be extracted by non-negative matrix factorization (NMF) in the previous study [32]. Then, the muscle synergy pattern will be converted into the FES stimulus envelope according to the conversion formula proposed by Niu [11].

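### Stratifying on dominant hand does not balance whether the affected arm is the dominant one; that is left to chance, and the planned adjustment does not include it

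*Protocol article*

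**What the plan says.** The section on randomization, allocation concealment and blinding in the protocol article uses "stratified randomization with sex (male/female), stroke type (hemorrhage/infarction) and dominant hand (left/right) as factors". It then states: "After categorization, there will be eight subgroups". All eight are listed, and four of them are left-hand dominant. Within strata, "For any one subgroup, the participants will be randomly divided into groups A, B, and C"; the overall allocation is "at a ratio of 1:1:1".

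The inclusion criteria admit "patients with unilateral right or left-sided stroke". Side is not a stratification factor, and no section crosses it with handedness.

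The robot is strapped to the affected limb (Robotic-assisted therapy section). RTG movements are assessed on the affected limb, with EMG from the same side (Biomechanical assessment section). The stimulation template has another origin: "The raw EMG signals of the dominant upper limb muscle will be obtained from healthy controls performing the RTG task".

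Under Statistical analysis, the adjusted model contains age, sex and stroke type, and is used only if homogeneity is not found. Neither handedness nor affected side is named there.

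**The concern.** In a trial that treats and measures the affected arm, handedness is relevant mainly through whether that arm is the dominant one. A right-hander with right-arm paresis and a right-hander with left-arm paresis fall in the same stratum, so the factor does not separate the two cases.

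If dominance of the affected arm influences recovery or drinking-task kinematics, an uneven split between groups would add noise to the comparisons in Aim 3, and no planned covariate would absorb it. The factor also reserves half of the declared strata for left-handers, who are likely to be few.

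**Working it through.** **Plan's own figure.** 129 / (1 - 0.20) = 161.25, rounded up to 162 = 3 × 54. This agrees with the Sample size calculation section: "the final sample size will therefore be 54 participants in each group, for a total of 162 participants". Strata: 2 × 2 × 2 = 8, also as stated.

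**Step 1: does stratifying on handedness balance dominance of the affected arm?** Let L be the proportion of left-handers and s the proportion with the right arm affected, and assume side is independent of handedness. Then the proportion with the dominant arm affected is p = (1 - L)s + L(1 - s). The share of its variance removed by stratifying on handedness is 1 - s(1 - s) / [p(1 - p)].

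- s = 0.50, any L: p = 0.50, share removed 0%.
- s = 0.55, L = 0.05: share removed 0.2%.
- s = 0.55, L = 0.10: p = 0.54, and 1 - 0.2475/0.2484 = 0.4%.

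The variable is therefore left almost entirely to chance.

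**Step 2: how large can the chance imbalance be?** With 54 per group and p = 0.5 (assumption), the SD of a difference between two groups is √(2 × 0.25 / 54) = 0.096, or 9.6 percentage points. Simulating three independent binomial counts of 54 gives:

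| Difference at least | A given pair, p = 0.5 | Largest of three pairs, p = 0.5 | Largest of three pairs, p = 0.4 |
|---|---|---|---|
| 10 points | 29% | 54% | 53% |
| 15 points | 10% | 23% | 22% |
| 20 points | 4% | 11% | 10% |

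**Step 3: how full are the left-handed strata?** Expected size = 162 × L × P(stroke type) × P(sex). The documents give none of these proportions. Assumptions: 60% men, 20-30% hemorrhage, 5-10% left-handers.

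| Left-handed | Hemorrhage | Men, hem. | Women, hem. | Men, inf. | Women, inf. | Total |
|---|---|---|---|---|---|---|
| 5% | 20% | 1.0 | 0.6 | 3.9 | 2.6 | 8.1 |
| 5% | 30% | 1.5 | 1.0 | 3.4 | 2.3 | 8.1 |
| 10% | 20% | 1.9 | 1.3 | 7.8 | 5.2 | 16.2 |
| 10% | 30% | 2.9 | 1.9 | 6.8 | 4.5 | 16.2 |

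Each cell is then split over three groups. At 5% left-handers and 20% hemorrhage, the two hemorrhage strata are empty with probability 38% (men) and 52% (women).

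**Step 4: the alternative factor.** With *affected arm is the dominant arm (yes/no)* in place of handedness, the same sex and stroke-type mix and 40-50% dominant-affected, there are still eight strata. The smallest expects 162 × 0.4 × 0.2 × 0.4 = 5.2 patients at one end of the range and 162 × 0.4 × 0.3 × 0.5 = 9.7 at the other. The largest expects up to about 47.

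**The case against.** The strongest reply is that nothing here is an error. The three factors match the eight listed strata, and a covariate outside the stratification is handled by randomisation, with its chance imbalance already reflected in the type I error and confidence intervals. That stands. A reader might infer that the groups will be unbalanced, or that the FES contrasts are confounded with dominance. The documents do not support this; they support only that the split is left to chance.

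Second, no section says that dominance of the affected arm changes FMA-UE recovery, RTG performance or the fit of the template. That the template comes from the dominant limb of healthy controls invites the inference that it fits a non-dominant limb worse, but the protocol does not say so. It gives no reason for choosing dominant hand as a factor either. This stands too.

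Third, the effect on a contrast is imbalance × dominance effect. To shift FMA-UE by 1 point, an imbalance of 15-20 points needs a dominance effect of 1/0.15 = 6.7 to 1/0.20 = 5 points, more than the 4.25-point clinically significant difference cited for the sample size. A 2-point effect (assumption) gives 0.3-0.4 points. A constant level difference also cancels from the group-by-time interaction; only a different trajectory would matter there. This limits the size, though the plan also tests the main effect of group, from which a level difference does not cancel.

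Fourth, it is tempting to call all four left-handed strata nearly empty. That holds only at about 5% left-handers or fewer. At 10%, the two infarction strata expect about 4.5-7.8 patients. The 90-95% who are right-handed keep their balance on sex and stroke type in any case.

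Finally, further covariates could be set in an analysis plan that is not shown. But the article does name its adjustment set, and this variable is not in it.

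**Conclusion.** The point holds as a moderate-to-minor weakness of design, not as a bias. The chosen factor removes at most about 0.4% of the variance of the dominance variable that concerns the treated and measured arm (side independent of handedness, at most 55:45, at most 10% left-handers), and the named covariates do not make up for it.

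Assuming half of the patients have the dominant arm affected, some pair of groups differs by at least 15 points in about 23% of trials and by at least 20 points in about 11%. What this does to FMA-UE or RTG cannot be derived from the documents.

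The two left-handed hemorrhage strata are sparse throughout the assumed range (about 0.6-2.9 patients each). The two left-handed infarction strata are sparse only at about 5% left-handers or below. The point is worth acting on because the main remedy costs almost nothing.

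**What to change.** **Main change, Statistical analysis section.** Derive *affected arm is the dominant arm (yes/no)* from handedness and affected side at T1 for every participant. Prespecify it as a baseline covariate in the FMA-UE and RTG models, whether or not groups appear homogeneous. Including its interaction with time is preferable, since only a different trajectory can disturb the group-by-time test. Both source variables are known before allocation: handedness is already a stratification factor, and side is checked at eligibility. The cost is one sentence in the plan and a few degrees of freedom.

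**Optional change, Randomization section.** Recruitment began on 1 May 2023. If enough of it remains, replace dominant hand by the derived variable for participants not yet randomised, keeping eight strata. This needs an amendment and a new envelope list, and part of the sample will have been randomised under the old strata. If that is not practical, the covariate alone is sufficient.
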